#### Patient-reported outcomes and biosignals

2.9.4

Health-related quality of life will be assessed using the AFEQT, a validated, disease-specific instrument for AF (38). The AFEQT comprises 20 items across four domains (Symptoms, Daily Activities, Treatment Concerns, and Treatment Satisfaction) with an overall score (0–100) derived from the first three domains; higher scores indicate better quality of life. A change of ⩾5 points is generally considered clinically meaningful (13). The AFEQT will be administered at baseline and follow-up to assess changes in AF-related symptoms and the broader impact of management strategies on daily life. To complement the AFEQT, participants will complete brief, rotating weekly questions aligned with the ESC quality of treatment indicators (31), assessing symptom status, physical functioning, emotional well-being, cognitive function, and knowledge of AF-related risk factors. Each question will be administered once per week to minimize participant burden.

All PROMs and biosignals will be collected via the chatbot. Body mass, blood pressure, and heart rate will be self-reported daily for the first four weeks and weekly thereafter, with blood pressure and heart rate measured using a blood pressure monitor. Physical activity will be tracked as daily step counts via the smartphone pedometer. Symptoms, including palpitations, dyspnea, chest pain, dizziness/syncope, fatigue, puncture-site changes, and edema, will also be reported daily during the first four weeks and weekly thereafter. To mitigate self-report bias, participants receive standardized training on device use and measurement technique at enrollment.

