The primary objective of this pilot study is to evaluate the feasibility and acceptability of integrating PROMBot-HSM-AF, a chatbot-based platform for collecting PROMs and clinical parameters, into routine post-ablation follow-up care at a tertiary hospital. The specific aims, framed for the feasibility and pilot phase, are to: (1) quantify recruitment, retention, and engagement rates over the 3-month follow-up and compare each against pre-specified progression thresholds (retention ⩾80%, engagement ⩾70%), constituting the primary outcomes; and, as secondary, exploratory outcomes, (2) assess the usability and acceptability of the chatbot (patients) and of the clinical monitoring interface (healthcare professionals) at 3 months, using validated usability measures (System Usability Scale [SUS], Post-Study System Usability Questionnaire [PSSUQ]), behavioral indicators, and semi-structured interviews; and (3) evaluate the preliminary integration and data completeness of PROMs (e.g., Atrial Fibrillation Effect on Quality-of-Life [AFEQT]) collected via the platform over the 3-month follow-up, and explore between-group differences as hypothesis-generating estimates to inform a definitive trial.

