#### PROMBot-HSM-AF platform intervention

2.7.1

The research team will configure the PROMBot-HSM-AF chatbot and related remote monitoring platform, including definition of finite-state dialogue flows with AF-specific questions, message content, and input-validation rules. Pilot testing with 2–3 test users will also be conducted to identify usability issues and to verify delivery, latency, and data integrity. Health professionals involved in recruitment and follow-up will receive training on study procedures, including informed consent, platform registration, and use of the clinician interface to monitor incoming data.

Eligible patients undergoing AF ablation will be approached during their hospital stay. After receiving written study information, discussing questions, and providing informed consent, participants will complete a baseline assessment that will include demographics, medical history, recent clinical parameters (e.g., blood pressure and heart rate), and health-related quality of life (AFEQT, European Portuguese version) (13, 30). For participants randomized to the intervention group, PROMBot-HSM-AF will be set up before discharge by confirming WhatsApp is installed on the participant’s smartphone, registering the participant in the remote monitoring platform, linking their mobile number to PROMBot-HSM-AF, and sending a confirmatory message to verify correct enrollment. Patients (and caregivers, if applicable) will receive a brief demonstration and training, delivered by the study nurse, to ensure they can interact with the chatbot autonomously, and will also receive a leaflet with a brief explanation of the chatbot.

Participants in the intervention group will engage with PROMBot-HSM-AF via chatbot for 12 weeks. The chatbot will request self-reported health metrics (e.g., body mass, blood pressure, heart rate, step count, AF-related symptoms) and general well-being, supplemented with brief educational prompts (31). Participants who do not already own a validated blood pressure monitor will be provided with one at enrollment; device ownership is assessed during the baseline visit.

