In the first month, chatbot interactions will occur daily, focusing on post-ablation symptom surveillance and medication adherence. After that, the cadence will taper to reduce burden in later weeks while maintaining essential monitoring. Chatbot prompts will remain open for 24 h, after which nonresponses will be recorded as missing data. A study nurse or physician will review patient entries weekly and may proactively contact participants reporting concerning symptoms or lapses in engagement. PROMBot-HSM-AF will not replace routine follow-up; all patients will continue standard clinical care, with chatbot data available to the study clinical team to complement or inform consultations at the treating cardiologist’s discretion.

At the end of the 3-month follow-up period, all participants will undergo post-intervention assessments during a routine hospital visit. If necessary, these assessments will be conducted via secure videoconference. The PROMs will focus on the effect of AF on health-related quality of life. Participants in the intervention group will also complete validated measures of usability and perceived usefulness. They will also take part in a brief semi-structured interview to share their experience of using the chatbot. Semi-structured interviews will also be conducted with healthcare professionals directly involved in patient care (e.g., cardiologists, nurses, and technicians). These interviews are intended to elicit qualitative insights regarding their experience with the chatbot-based intervention, as well as their perceptions of its usability, clinical relevance, and impact on workflow integration.

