#### Control group

2.7.2

Participants allocated to the control group receive standard post-ablation care as delivered at Santa Marta Hospital, which includes structured discharge instructions with written educational materials about post-ablation care, scheduled follow-up appointments at 1 month and 3 months post-discharge, open access to the cardiology clinic telephone line during working hours for clinical concerns, and a 24-h hospital telephone service for urgent medical issues. Control group participants do not receive remote monitoring between scheduled appointments.

Both intervention and control groups complete identical standardized assessments at baseline (pre-discharge) and 3 months post-ablation. The timing of data collection activities is outlined in Table 1.

**Table 1 T1:** Schedule of enrollment, interventions, and assessments for the PROMBot-HSM-AF trial.

TRIAL PERIOD		Enrollment	Post-randomization				
Timepoint	Arm	⩽ day 0	Day 0	M1	M2	M3	M12
Target window		up to day 0	day 0	30±3 d	60±5 d	90±5 d	365±14 d
ENROLLMENT							
Eligibility screen	I+C	X					
Informed consent	I+C	X					
Randomization/allocation	I+C		X				
INTERVENTIONS							
PROMBot-HSM-AF	I			X	X	X	
Standard care	C		X	X	X	X	
PRIMARY OUTCOMES (FEASIBILITY)							
Recruitment rate	I+C	X	X				
Retention rate	I+C					X	
Engagement rate	I			X	X	X	
BASELINE CHARACTERISTICS							
Demographics	I+C		X				
AF history & comorbidities	I+C		X				
Procedure-related characteristics	I+C		X				
CLINICAL OUTCOMES (HOSPITAL-REPORTED)							
AF recurrence (AAD/cardioversion/repeat ablation)	I+C			X	X	X	X
Complications (readmission, ED visit, thromboembolism, major bleeding, tamponade)	I+C			X	X	X	X
All-cause mortality	I+C						X
Cardiology/internal-medicine consultations	I+C					X	X
Diagnostic tests (ECG, Holter)	I+C			X	X	X	X
PROMs							
AFEQT	I+C		X			X	
ESC quality-indicator items (weekly, rotating)	I			X	X	X	
Symptom checklist	I			X	X	X	
Medication adherence	I			X	X	X	
BIOSIGNALS							
Body mass	I			X	X	X	
Blood pressure	I			X	X	X	
Heart rate	I			X	X	X	
Step count	I			X	X	X	
ACCEPTABILITY & USABILITY							
Patient experience (SUS, PSSUQ, interview)	I					X	
Healthcare-professional experience (SUS, PSSUQ, interview)	HCP					X	

The schedule follows the SPIRIT figure convention (34).

M, month; d, days. Arm: I = intervention; C = control; HCP = healthcare professionals.

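### Section 2.9.4 and aim 3 route the AFEQT through the chatbot, which Table 1 and Sections 2.5 and 2.7 rule out for controls and at baseline; using it at month 3 in one arm could bias the comparison

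*Protocol article*

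**What the plan says.** The protocol article describes two routes for the same questionnaire.

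**Chatbot route.** Section 2.9.4 introduces the AFEQT and then says, with no exception, "All PROMs and biosignals will be collected via the chatbot". Aim 3 in the Introduction gives the AFEQT as its example of PROMs "collected via the platform over the 3-month follow-up", and in the same aim asks for between-group differences to inform a definitive trial.

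**Visit route.** Section 2.7.1 includes the AFEQT in the in-hospital baseline assessment. For month 3 it says "all participants will undergo post-intervention assessments during a routine hospital visit", with videoconference as a fallback, and the same paragraph adds: "The PROMs will focus on the effect of AF on health-related quality of life". Section 2.7.2 says: "Both intervention and control groups complete identical standardized assessments at baseline (pre-discharge) and 3 months post-ablation". Table 1 lists the AFEQT for intervention and control at day 0 and month 3.

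**Who has the chatbot.** Section 2.7.1: "For participants randomized to the intervention group, PROMBot-HSM-AF will be set up before discharge". Section 2.7.2: "Control group participants do not receive remote monitoring between scheduled appointments". Section 2.5 has the allocation envelope opened only once the baseline assessments are done.

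**The concern.** The AFEQT is the only PROM that Table 1 schedules in both arms, and the study hypothesis in Section 2.1 names it. It is therefore the only patient-reported measure on which the arms can be compared. Staff who follow Section 2.9.4 and staff who follow Section 2.7 would collect it differently.

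If the intervention arm answered by WhatsApp at month 3 while controls answered at the hospital, any effect of mode or setting on the score would be part of the between-group difference. If everyone answered at the visit, aim 3 would have no AFEQT data from the platform on which to judge completeness. On either route, one stated element of the plan fails.

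**Working it through.** The article gives no figure to reproduce, so the check is mainly a comparison of text.

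**1. Does the Section 2.9.4 sentence cover the AFEQT?** By the article's own classification it does. Table 1 places the AFEQT under PROMs, Section 2.9.4 defines it in the paragraph just before the sentence, and aim 3 names it as platform-collected.

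**2. Can the chatbot rule be followed in each arm at each time?**

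| Arm | Time | Chatbot possible? | Reason |
|---|---|---|---|
| Control | Day 0 | No | Set-up is for the intervention group only (2.7.1) |
| Control | Month 3 | No | Same, and no remote monitoring (2.7.2) |
| Intervention | Day 0 | No | Baseline AFEQT (2.7.1) precedes envelope opening (2.5), hence precedes set-up |
| Intervention | Month 3 | Yes | But this conflicts with the visit for all (2.7.1) and identical assessments (2.7.2) |

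The rule fails in three of the four cells. In the fourth it contradicts two other sections.

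**3. What follows if the fourth cell uses the chatbot?** Let D be the true difference in mean month 3 AFEQT, and m the shift in mean score caused by chatbot rather than visit completion.

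- Different modes by arm: expected difference = D + m.
- Same mode in both arms, with m the same in each: expected difference = (D + m) − m = D.

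No control can answer by chatbot, so the trial data cannot estimate m. Adjusting for baseline AFEQT, as the regression models in Section 2.10.1 might, does not remove m, because baseline is taken before anyone has the chatbot. Change from baseline within the intervention arm would contain m as well.

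Section 2.7.1 also records unanswered chatbot prompts as missing after 24 h. If the AFEQT were sent as such a prompt, the intervention arm would have a missing-data rule that cannot apply to controls.

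**4. What follows if the visit route is used?** Step 3 does not arise. Aim 3's AFEQT completeness via the platform then has nothing to measure.

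**5. Scale.** The article gives 5 points as a clinically meaningful AFEQT change. It gives neither an SD nor any figure for a mode effect. For precision only, assume an SD of 15 to 25 and 38 × 0.8 = 30.4, taken as 30 per arm, after the 20% dropout allowed in Section 2.4. With SE = SD × √(2/30) and half-width = 1.96 × SE:

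- SD 15: SE 3.87, 95% CI half-width 7.6 points
- SD 20: SE 5.16, half-width 10.1 points
- SD 25: SE 6.45, half-width 12.7 points

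These figures say nothing about m. They show that the interval would be wide on either route. A mode shift would add to the difference in full and would not shrink with sample size.

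**The case against.** The strongest defence is that the sentence is loose wording for the chatbot-only measures. It opens the paragraph on daily and weekly self-reports, whereas the AFEQT is defined in the paragraph before, with the timing "The AFEQT will be administered at baseline and follow-up to assess changes in AF-related symptoms". Table 1 marks the ESC items, symptoms, adherence and biosignals as intervention only, and the AFEQT as both arms. The operational sections point to the visit. This may well be what the sponsor intends, but the text does not say so, and aim 3 names the AFEQT as platform-collected. The wording conflict stands.

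A second defence is that little depends on the result. The AFEQT is secondary and exploratory, the Discussion says that clinical comparisons are not evidence of effectiveness, and no primary outcome or progression threshold uses it. That is right and limits the weight of the point. It does not remove it, since aim 3 intends these estimates to inform a definitive trial.

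A reader might infer more than the document supports, in three ways:

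- *That the AFEQT difference will be biased.* No passage says that the month 3 AFEQT is actually taken by WhatsApp in one arm and at the visit in the other. The bias is conditional on that.
- *That the 70% engagement threshold predicts how many intervention patients return an AFEQT.* Engagement is a proportion of prompts over 12 weeks, not the chance that a patient completes one form, and 70% is a progression minimum. No passage says that the AFEQT is sent as a 24 h prompt. Intervention patients also attend the month 3 visit, and dropout is allowed for overall, so full control attendance cannot be assumed.
- *That a particular number of points can be put on the mode effect.* The document offers no basis for one.

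**Conclusion.** The contradiction holds and depends on no assumption: as written, the chatbot rule cannot be followed for the AFEQT in three of four arm-by-time cells, and in the fourth it conflicts with Sections 2.7.1 and 2.7.2. The bias is a conditional consequence. If the chatbot is used for intervention patients at month 3, mode and setting are fully confounded with arm, as is the non-response rule if the AFEQT is sent as a prompt. The exploratory AFEQT difference could then be biased by an unknown amount and in an unknown direction.

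The importance is moderate. The outcome is exploratory, but it is the only PROM shared by the arms, and confounding of this kind cannot be undone once the data are collected. It should be settled before further month 3 assessments take place. This is not detail left to a fuller document: the article states the collection route, and states it in two incompatible ways.

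**What to change.** 1. In Section 2.9.4, limit the sentence to the measures that Table 1 schedules in the intervention arm only: ESC items, symptoms, medication adherence and biosignals.
2. State that the AFEQT used for the between-group comparison is completed in both arms in the same mode and within the same window at the baseline and month 3 visits, with the same video fallback at month 3. Record the mode actually used for each form.
3. In aim 3, base platform completeness on the chatbot-only measures.

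If the sponsor wishes to keep the AFEQT by chatbot in one arm, the article should say so and state the mode difference as a limitation of the comparison.

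The cost is wording in two or three places and a form at visits that already exist. The real downside is that the trial would yield no figure for AFEQT completeness by chatbot. That alters part of a stated aim, so the sponsor should make the choice deliberately.

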#### Chatbot system usability and perceived usefulness

2.9.5

The usability and acceptability of the system will be assessed using the System Usability Scale (SUS), a widely adopted 10-item self-administered questionnaire that generates a global usability score ranging from 0 to 100. Scores above 68 are generally interpreted as reflecting good usability. The European Portuguese version has been translated, culturally adapted, and validated, demonstrating good construct validity through significant correlations with the PSSUQ (r=0.70) and with a general usability item (r=0.48) (39). User satisfaction and perceived usefulness will be evaluated using the Post-Study System Usability Questionnaire (PSSUQ), a 19-item scale validated in European Portuguese, which has shown excellent internal consistency (a=0.80), satisfactory inter-rater reliability (ICC = 0.67), and strong construct validity (r=0.84, P<.05) (40). In this instrument, lower scores indicate greater satisfaction. Both SUS and PSSUQ will be administered at follow-up to provide a comprehensive evaluation of participants’ (patients and health professionals) experiences with the PROMBot-HSM-AF intervention.

To complement quantitative assessments, semi-structured interviews will be conducted with patients (see Supplementary Table S1) to qualitatively explore their experiences with PROMBot-HSM-AF. Healthcare professionals directly involved in patient care (e.g., cardiologists, nurses, and technicians) will also participate in semi-structured interviews (see Supplementary Table S1) to provide insights into usability, workflow integration, perceived utility, time burden, and potential improvements.

### Data analysis

2.10

This study will employ a mixed-methods approach, combining quantitative and qualitative data from both patients and health professionals, to enable a comprehensive evaluation of the intervention’s outcomes and implementation processes, consistent with recommended mixed-methods approaches for feasibility trials (27).

#### Quantitative data

2.10.1

Participant characteristics and study outcomes will be summarized using descriptive statistics. Continuous variables (e.g., age, body mass, blood pressure) will be reported as means ± SDs or medians [IQR], depending on distribution, while categorical variables (e.g., sex, educational level, comorbidities) will be expressed as frequencies and percentages. Comparisons between groups will be performed using independent t-tests or Mann-Whitney U tests for continuous variables, and chi-square or Fisher exact tests for categorical variables, with 95% confidence intervals reported. The effect of the intervention on primary and secondary AF-related outcomes will be examined using regression models with and without adjustment for baseline covariates. Formal hypothesis testing is not the primary focus. All analyses will be conducted in R (version 4.5.0), with statistical significance defined as a two-sided p-value <0.05.

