### Randomization and allocation concealment

2.5

Participants will be randomly assigned to the intervention or control group using computer-generated random numbers in permuted blocks of variable size (4 to 6) to maintain allocation concealment. Randomization will be stratified by AF type (paroxysmal vs persistent) to ensure balance between groups, as AF type is a recognized prognostic factor for recurrence after catheter ablation (29). Allocation sequences will be generated by a statistician not involved in participant recruitment. Allocation concealment will be maintained through sequentially numbered, opaque, sealed envelopes prepared by personnel independent of the recruitment process, opened only after eligibility confirmation and completion of baseline assessments.

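### No main AFEQT analysis is designated: the named two-sample tests use neither baseline AFEQT nor AF type, and the planned adjusted regression has no covariates named and no priority

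*Protocol article*

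**What the plan says.** Section 2.10.1 (Quantitative data) lists two sets of between-group methods.

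- **Two-sample tests.** "Comparisons between groups will be performed using independent t-tests or Mann-Whitney U tests for continuous variables". Categorical outcomes get their own pair of tests, also without any adjustment: "chi-square or Fisher exact tests for categorical variables, with 95% confidence intervals reported".
- **Regression.** The intervention effect on the AF-related outcomes "will be examined using regression models with and without adjustment for baseline covariates". No covariate is named, and neither version is given precedence.

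The section adds "Formal hypothesis testing is not the primary focus", yet keeps "statistical significance defined as a two-sided p-value <0.05".

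Three other places bear on the point.

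- Section 2.5: "Randomization will be stratified by AF type (paroxysmal vs persistent) to ensure balance between groups". The reason given is that AF type is prognostic for recurrence after ablation.
- Section 2.9.4: "The AFEQT will be administered at baseline and follow-up to assess changes". Section 2.7.2 and Table 1 confirm that both arms complete it at baseline and at 3 months. The same section treats a change of 5 points or more as clinically meaningful.
- Introduction, aim 3: between-group differences are hypothesis-generating estimates meant to inform a definitive trial.

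**The concern.** Aim 3 needs a usable estimate of the AFEQT difference and the variance quantities for sizing the next trial. The analysis section does not say which result supplies them.

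- The t-test discards the baseline score, which usually predicts the 3-month score.
- The Mann-Whitney test does not estimate a mean difference at all.
- Neither test returns a residual SD after baseline adjustment.
- Section 2.9.4 speaks of assessing changes, but section 2.10.1 does not say whether the two-sample test compares 3-month scores or change scores. That choice also alters the precision.
- The adjusted regression could supply what is needed, but it stands level with the unadjusted one.

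With about 30 to 38 patients per arm, precision is scarce. Choosing among the results after seeing them would weaken the estimate carried forward.

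**Working it through.** **The plan's own figure.** There is none to reproduce. Section 2.4 sizes the trial on retention and engagement, and the document gives no SD, correlation, precision or power for AFEQT.

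**Inputs from the document.** 38 per group and 20% dropout (section 2.4), so 38 × 0.8 = 30.4, taken as 30 completers per arm. Meaningful change of 5 points (section 2.9.4).

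**Assumptions.** AFEQT SD of 20 (range 15 to 25), and a correlation ρ between baseline and 3-month AFEQT of 0.3, 0.5 or 0.7.

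**Formulas for the 95% CI half-width, n per arm.**

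- Unadjusted 3-month score: t(2n−2) × SD × √(2/n)
- ANCOVA on baseline and stratum: t(2n−4) × SD × √(1−ρ²) × √(2/n)
- Change score: t(2n−2) × SD × √(2(1−ρ)) × √(2/n)

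**Worked case, n = 30, SD 20, ρ = 0.5.** SD × √(2/n) = 20 × √(2/30) = 5.164.

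- Unadjusted: 2.002 × 5.164 = 10.3
- ANCOVA: 2.003 × 5.164 × 0.866 = 9.0

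**Results for SD 20 (points).**

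| n per arm | Analysis | ρ = 0.3 | ρ = 0.5 | ρ = 0.7 |
|---|---|---|---|---|
| 30 | Unadjusted | 10.3 | 10.3 | 10.3 |
| 30 | ANCOVA | 9.9 | 9.0 | 7.4 |
| 30 | Change score | 12.2 | 10.3 | 8.0 |
| 38 | Unadjusted | 9.1 | 9.1 | 9.1 |
| 38 | ANCOVA | 8.7 | 7.9 | 6.5 |

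At 30 per arm, for SD 15 to 25, the unadjusted half-width runs from about 7.7 to 12.9, and ANCOVA at ρ = 0.5 from 6.7 to 11.2. A change-score comparison beats the unadjusted 3-month comparison only when ρ exceeds 0.5.

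**Residual SD for sizing.** SD × √(1−ρ²) = 19.1, 17.3 and 14.3 at ρ = 0.3, 0.5 and 0.7. Required sample size scales with 1−ρ², that is 0.91, 0.75 and 0.51 of the unadjusted figure.

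**Where the gain comes from.** This was checked by simulation: 8,000 runs, 30 per arm, SD 20, two equal strata balanced across arms, and an assumed 10-point stratum effect.

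| ρ | Unadjusted half-width (coverage) | Adjusted half-width (coverage) |
|---|---|---|
| 0 (stratum only informative) | 10.6 (0.956) | 10.4 (0.948) |
| 0.5 | 10.6 (0.956) | 9.0 (0.951) |

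The stratum alone moves the half-width by about 0.2 points. Baseline AFEQT accounts for nearly all the rest. The unadjusted interval remains valid and is at most slightly conservative.

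**The case against.** The strongest reply is that adjustment is already in the plan. The two-sample test sentence is generic, and the next sentence examines the intervention effect by "regression models with and without adjustment for baseline covariates". Baseline AFEQT and AF type are both collected and may be among those covariates, and a full analysis plan, not shown here, may name them. This stands: the plan does not omit adjustment, and a missing covariate list alone would not be a finding. What remains is what the article does fix: unadjusted and rank-based tests as named comparisons, and two regressions of equal standing.

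Several stronger readings are tempting, but the document does not support them.

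- *That precision will be lost.* The figures compare an unadjusted with an adjusted main estimate. Since the adjusted one may be run anyway, they show what is at stake in the choice, not a certain loss.
- *That ignoring the stratum makes the intervals wrong.* Simulated coverage is about 0.95 to 0.96. AF type is called prognostic for recurrence, not for AFEQT.
- *That clinical-outcome intervals are also too wide.* No calculation shows it. These outcomes have no baseline AFEQT analogue, and covariate adjustment in a logistic model does not generally narrow the interval for the log odds ratio.
- *That three different mean differences compete.* An equal-variance t-test and an unadjusted linear regression on arm give the same difference. A third answer arises only if the rank test is used.
- *That the test is chosen by looking at the data.* In section 2.10.1, dependence on distribution is stated for the descriptive summaries only. Carrying it over to the tests is a plausible inference, not the text.

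The stakes are also limited. The trial is sized for feasibility, the Discussion calls the clinical comparisons exploratory, and no progression threshold uses them.

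**Conclusion.** The point holds for AFEQT, as a choice of main analysis. Section 2.10.1 leaves the main estimate open among methods that differ in precision and, for the rank test, in what they estimate. Under an assumed SD of 20 and 30 completers per arm, making the adjusted analysis the main one takes the half-width from 10.3 points to about 9.9, 9.0 or 7.4 at ρ = 0.3, 0.5 or 0.7. That is equivalent to 1.10, 1.33 or 1.96 times the sample size, from 1/(1−ρ²). All of these half-widths exceed the 5-point meaningful change, so AFEQT stays imprecise either way. The benefit is a tighter, pre-designated estimate and the right inputs for sizing, not a conclusive comparison. For binary clinical outcomes the only argument is consistency with the stratified randomisation, and no precision gain is claimed. Priority is low to moderate, because the comparisons are exploratory and no feasibility conclusion depends on them.

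**What to change.** In section 2.10.1, designate one main analysis for AFEQT: ANCOVA of the 3-month overall score on arm, baseline AFEQT and AF type. Report the adjusted mean difference with its 95% CI, the residual SD, and the correlation between baseline and 3-month scores. Label the unadjusted and rank-based results as sensitivity analyses.

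For binary clinical outcomes, account for AF type where event counts allow, for example with a Mantel-Haenszel risk difference stratified by AF type. Give consistency with the stratified randomisation as the reason.

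The cost is a change of wording. Every variable is already collected, and neither the sample size nor the visit schedule changes.
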